## DESIGN AND PROCESS OF INTRODUCING PREP DELIVERY IN FP CLINICS

Systematic integrated screening for HIV risk and counseling for and provision of PrEP will be introduced and actively promoted in family planning clinics in Kisumu. These strategies will be introduced in staged three successive waves (steps), occurring every 3 months, with 4 clinics per step or stepped-wedge design (**Figure 2**). The order at which clinics initiate the implementation will be determined

[figure not shown]

by randomization stratified by clinic size, identified as likely to have a marked effect on implementation outcome. Randomization process will take place at a meeting with the Kisumu County Health leadership, implementing health facilities and led by the project staff. Prior to initiating implementation of the program, we will conduct clinic-wide training for health providers at each clinic and we will engage existing FP providers in continuous quality improvement to optimize delivery. At all implementing clinics, we will conduct a pre-implementation needs assessment and observation of current services to optimize data and PrEP supply systems. During this pre-implementation period, a minimum of 3 months for each clinic, we will assess and document current processes on HIV counseling and testing, male partner testing, PrEP counseling and use (expected to be minimal), STI counseling and treatment, male partner STI testing and treatment of women infected with STIs, incident HIV and STI. During implementation, we will optimize delivery of PrEP in combination HIV prevention using existing FP clinic staff supported through ongoing technical assistance from program technical team and MOH/NASCOP and Kisumu County Health supervision team to audit for process indicators of implementation progress and continuation quality improvement. On-the-job training of new staff will be promoted and we will conduct refresher CME-like training quarterly or as needed.

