PrEP technical assistance and county supervision: We will conduct ongoing technical assistance to clinics using trained program nurses to coach, mentor, and guide FP clinics to troubleshoot emerging challenges with integrating new services. Technical advisors (TA) will be project nurses with training in PrEP delivery. Prior to implementation, Program nurses will undergo an intensive 2 weeks didactic and protocol training conducted by study investigators, in collaboration with Kenya MOH and Kisumu Health officials. TA will conduct structured periodic visits to each clinic to coach and mentor the health care providers and observe and document PrEP implementation processes with a specific focus on processes that are effective or not and aspects of delivery that are changing with time. Using rapid-cycle analysis approaches, TAs will make summary reports at the end of each clinic visit highlighting what changed, why it changed, who initiated the changes, and outcome of any changes instituted. Best practices will be shared across all clinics for possible adoption. For the first 3 months post-introduction, study nurses (TAs) will visit clinics weekly for 3 months, and then complete monthly visits through the 12-month intensive implementation phase. During year 2, TA activities will scale back to observe sustainment phase. Throughout the first 18 months, the TAs will be accompanied to facility visits by County health and or Kenya MOH/NASCOP supervisors to audit for process indicators for FP services, HIV prevention services, and PrEP and progress.

Novel clinic and patient flow mapping: We will conduct workflow mapping at all sites to identify potential bottlenecks, differences and commonalities among sites at baseline and 6 monthly. We will solicit provider engagement in defining new flow maps to accommodate new tasks and patient flows. Current and future flow maps will be created for each site to demonstrate new pathways.

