periods of intensive care in baseline and steps 1-3 to estimate a relative risk (RR) for the outcome associated with implementation. We will estimate each RR using a generalized mixed model. The key predictor will be intervention status of the clinic during the step in which the participant is enrolled, as a fixed effect. The model will also include step, as a fixed effect, and clinic, as a random effect. The model may also include a random effect for step and for the intervention effect, if evidence in our data shows that these are in fact varying randomly and not fixed. The mixed model will generate RRs using a modified Poisson model (i.e. Poisson regression with robust error variance) with robust standard errors to allow valid estimation of SEs for log (RR) from Poisson regression, which is a very stable model compared to alternatives. Using Steps 3-4 vs 7-8 (see **Figure 2**), we will conduct secondary analyses using similar methods to estimate changes in outcome during the maintenance phase compared to the intensive phase to quantitatively ascertain level of institutionalization. We will also describe, over the steps, the proportion of clients screened for HIV prevention including HIV testing and PrEP counseling, to assure that the intervention is being implemented as expected and ensure that any increase in % screening for HIV risk observed, includes PrEP counseling as part of the standard package now reaching a larger proportion of women. For individual level data from open-cohort, descriptive analyses will be done at baseline and over time, and appropriate regression models (e.g., cox proportional hazards for survival outcomes, and generalized estimating equation for binary or count data) comparing clinical outcomes between women who initiated PrEP vs those who chose not to initiate PrEP, accounting for age, partner HIV status, repeated measures, time-dependent exposures, and clinic-clustering.

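### The secondary maintenance contrast (steps 3-4 against steps 7-8) makes phase coincide with calendar step, so the stated model cannot estimate it and any version without fixed step effects is confounded with time

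*Protocol*

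**What the plan says.** The section on analysis of quantitative data (Protocol, DATA) describes the main model as a generalised mixed model, fitted as modified Poisson, with the clinic's intervention status as a fixed effect. It adds: "The model will also include step, as a fixed effect, and clinic, as a random effect". It also allows a random effect for step and for the intervention effect if the data call for them. The main comparison contrasts usual care with "periods of intensive care in baseline and steps 1-3".

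The maintenance analysis follows in the same paragraph. It opens "Using Steps 3-4 vs 7-8", points to Figure 2, and continues: "we will conduct secondary analyses using similar methods to estimate changes in outcome during the maintenance phase compared to the intensive phase". Its stated purpose is to measure how far delivery has become institutionalised. Nothing is said about steps 5 and 6, about leaving step out of the model, or about time trends in this contrast.

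The timetable comes from two other places. The design section gives "three successive waves (steps), occurring every 3 months, with 4 clinics per step". The paragraph on technical assistance and county supervision has the nurses "complete monthly visits through the 12-month intensive implementation phase", and then: "During year 2, TA activities will scale back to observe sustainment phase".

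**The concern.** A stepped-wedge model separates an intervention effect from calendar time because, within some steps, clinics are in different states. The maintenance contrast uses only steps in which every clinic is in the same state. If step stays in the model as a fixed effect, nothing is left from which to estimate phase. If it does not, the comparison has no concurrent control and takes up whatever else changed over the year between the blocks. The protocol's literature review says that national PrEP delivery was slowly expanding, so a trend is plausible.

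Sustainment matters here. The hypothesis is about sustainable delivery by existing staff, and the background reports that PrEP delivery fell in the pilot once dedicated staff left. A rising background could hide a repeat of that decline in this analysis, and a falling one could suggest a decline that did not occur.

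**Working it through.** **Step numbering.** The protocol gives no figure for the maintenance contrast, but its sample size total fixes the numbering. 12 clinics × 100 women × 4 periods (baseline plus steps 1-3) = 4,800, the stated total. At 75 and 50 women per clinic-step the same product gives 3,600 and 2,400, as in Table 2. So wave *w* starts at step *w*.

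**Phase map.** Steps last 3 months, so a 12-month intensive phase is 4 steps. Wave *w* is intensive in steps *w* to *w*+3 and in maintenance from step *w*+4 (I = intensive, M = maintenance):

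| Step | 3 | 4 | 5 | 6 | 7 | 8 |
|---|---|---|---|---|---|---|
| Wave 1 | I | I | M | M | M | M |
| Wave 2 | I | I | I | M | M | M |
| Wave 3 | I | I | I | I | M | M |

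Trying intensive lengths of 1 to 6 steps, only 4 steps makes both chosen blocks uniform. The protocol's choice of blocks therefore agrees with its stated 12 months.

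**Identification.** In steps 3, 4, 7 and 8, the maintenance indicator equals the step-7 indicator plus the step-8 indicator. Rank of the design matrix (intercept, step indicators, phase, and clinic or wave terms where shown):

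| Data used | Terms | Columns | Rank |
|---|---|---|---|
| Steps 3, 4, 7, 8 | step + phase | 5 | 4 |
| Steps 3, 4, 7, 8 | step + wave + phase | 7 | 6 |
| Steps 3, 4, 7, 8 | step + clinic + phase | 16 | 15 |
| Steps 3, 4, 7, 8 | phase only | 2 | 2 |
| Steps 3-8 | step + phase | 7 | 7 |
| Steps 3-8 | step + wave + phase | 9 | 9 |
| Steps 3-8 | step + clinic + phase | 18 | 18 |

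With fixed step effects the planned contrast is one rank short however many women are included. Adding steps 5-6 restores full rank.

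**Size of the confounding if step is dropped.** The blocks are 4 steps apart. With a multiplicative trend *g* per step, the apparent RR is the true RR × (*g*⁷ + *g*⁸)/(*g*³ + *g*⁴) = true RR × *g*⁴. The protocol gives no trend, so *g* is an assumption:

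| *g* per step (assumed) | Apparent RR, true RR 1.00 | Apparent RR, true RR 0.80 |
|---|---|---|
| 0.95 | 0.81 | 0.65 |
| 0.98 | 0.92 | 0.74 |
| 1.02 | 1.08 | 0.87 |
| 1.05 | 1.22 | 0.97 |
| 1.10 | 1.46 | 1.17 |

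**Precision of the alternative.** Assume 100 women per clinic-step, 22% uptake, clinic and step effects, and binomial error only. The cell variance is 0.22 × 0.78/100 = 0.001716. On steps 3-8, the phase indicator adjusted for clinic and step has a sum of squares of 1 per set of three clinics (one from each wave), hence 4 over 12 clinics. The standard error is √(0.001716/4) = 2.1 percentage points. The before-after contrast without step has √(0.001716 × (1/24 + 1/24)) = 1.2 points. Extra variation between clinics would widen the first.

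**The case against.** Four points can be made for the plan.

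- *The analysis is secondary.* This stands. The co-primary outcomes are compared over baseline and steps 1-3. The protocol's defined maintenance measure is a count of clinics still delivering PrEP 6 and 12 months after intensive assistance ends, which needs no model. A reader might infer that the main result, or all evidence on sustainment, is compromised; the documents do not support that.
- *Similar methods need not mean the identical model, and a random step effect is allowed.* True, so non-estimability holds only if the fixed step effect is kept. But a random step in place of the fixed one makes the model fit while all information on phase still comes from two blocks of calendar time. No reading gives a controlled comparison. Nor is this a detail left to a SAP: the protocol itself fixes the steps and names the method.
- *Figure 2 is missing.* The map is inferred, and a 3-month interval is stated only for the roll-out waves. The match between the chosen blocks and the 12-month intensive phase makes another map unlikely, not impossible.
- *Leaving out mixed steps gives clean phases.* That is a fair reason to describe the two blocks. It does not make their difference attributable to phase.

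Two stronger readings are tempting. One is that any trend would pass for sustainment; only an upward one would. The other is that wave 3's first six months, which fall in steps 3-4, must flatter maintenance. Start-up could lower outcomes then, but those months also include the most frequent support visits, which could raise them. The documents do not settle the direction.

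**Conclusion.** The point holds for this secondary analysis. On the timetable in the text, the model with fixed step effects cannot estimate the maintenance effect from steps 3, 4, 7 and 8. Any version without fixed step effects is an uncontrolled before-after contrast about 12 months apart. Assumed trends between -5% and +10% per step would move a null effect to anywhere from RR 0.81 to 1.46. Those trends illustrate the exposure; they are not estimates of what happened in these clinics. The conclusion rests on wave *w* starting at step *w*, 3-month steps throughout, and a 12-month intensive phase in every clinic. It is a defect in how sustainment would be quantified, not in the trial's main comparison.

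**What to change.** Fit the maintenance model on steps 3 through 8, keeping step as a fixed effect and clinic as a random effect. Code phase for each clinic from the end of its own 12-month intensive period. Step 5 then sets 4 maintenance clinics beside 8 intensive ones, and step 6 sets 8 beside 4, in the randomised order of the waves.

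State the limits with it:
- The estimate reflects mainly the early change after handover. Maintenance clinics in steps 5-6 are at most six months past it, and the intensive comparators are in months 7-12 of support, by then on monthly visits.
- It assumes step effects common to all clinics and a constant phase effect.
- It does not separate phase from time since a clinic started.
- Its interval is wider than the before-after one: a standard error of about 2.1 against 1.2 points under the assumptions above.

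Report steps 3-4 against 7-8 as a descriptive before-after comparison, and draw no causal conclusion about institutionalisation from it. The cost is a change of analysis wording and some precision. No extra data collection should be needed, since steps 5-6 lie within the programme period, but the change should be made before these data are analysed.

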## HEALTH ECONOMICS STUDIES

We will conduct micro-costing studies during implementation of PrEP delivery in FP clinics and the current practice (baseline period) using activity-based approaches for costs incurred (start-up activities, clinic wide trainings, recruitment, PrEP service delivery, including HIV testing, PrEP drugs, STI treatment, creatinine testing, and follow-up) and direct program costs averted (health costs saved by averting HIV infections, personnel costs averted as result of providing FP and PrEP in one location). Program costs will also be collected from the study budget, public health clinic budgets, government reports, and the health economics literature, as we have done in previous work. The primary outcome will be the costs (incremental relative to current practice) for PrEP provision in FP clinics including HIV treatment costs averted as a result of preventing HIV infections.

Time and motion studies: We will conduct time and motion studies by observing clinical visits to assess staff time spent on counseling, HIV counseling and PrEP provision. We will conduct staff interviews to assess time spent on PrEP-related activities and its impact on other usual FP services. We will serially measure total time spent to deliver PrEP integrated in FP clinics compared to staff time spent to deliver FP services in clinics during baseline period (with current practice) and during implementation period. We will assess costs incurred by patients (opportunity and financial costs) to access FP and HIV service including PrEP counseling and provision through participant questionnaires.

**Decision analysis modeling:** We will use a dynamic transmission model to simulate HIV infection, informed by previous modeling work. The model will explicitly capture current and future HIV prevention methods mix and the impact of integrating PrEP delivery in FP clinics on incident HIV infections as well as impact on current FP services. The model will be programmed in Excel (Matlab). We will estimate primary study outcomes: the cost of PrEP provision per person and incident HIV infection averted annually relative to current FP services alone. Models will be used to simulate the number of HIV infection cases in the absence of an intervention as well as current service (condom use, partner testing, treatment as prevention, STI screening and treatment) and

potential future HIV prevention methods mix. Total program costs will be divided by the number of HIV cases averted annually. We will additionally estimate the long-term costs and health effects that cannot be accurately assessed during our tracking period – using adapted models and data from the study and the literature.

**Approach for estimating affordability and budget impact:** Using the intervention effectiveness, costing, and decision analysis from this study, the cost per incident HIV case averted will be estimated. Using data on the incremental cost of the intervention, we will assess the budget impact on the Kenya MOH and Kisumu County budgets for including the interventions, incorporating the eligible population size, and current MOH and Kisumu budget expenditures. We will consider direct program costs, to ensure that measurements of MOH costs reflect the opportunity cost of the resources used in delivering services. The primary analysis will be from the *programmatic perspective* and secondary analysis from the *societal perspective* to account for users' financial and opportunity costs of accessing services. To the extent possible, we will use guidelines to facilitate standardization of cost data collection and reporting. This approach will also increase the transparency and generalizability of our results. For all key inputs and outputs, we will follow standard practices, including the guidelines by the Panel of Cost-Effectiveness in Health and Medicine. The primary analysis costs will be undiscounted inputs. Beyond scope of this grant, the unit costs estimated will provide the basis for more sophisticated cost-effectiveness analyses of the approaches in Kenya, for policy decision makers and payers.

### **QUALITY ASSURANCE PROCEDURES**

All program procedures will be implemented in accordance with the MoH protocols and guidelines. All data will be maintained in a secure location. Internal quality control reports will be run on a monthly basis to monitor program progress, discussed with clinics, MOH/ NASCOP and County Health leadership to improve implementation as the program comes to full scale.

### **DISSEMINATION**

We will disseminate outcomes of M & E activities to national and international stakeholders and facilitate technical assistance for PrEP scale-up in other settings. Our finalized PrEP delivery model for women will be collated in stakeholder consultations and training programs coordinated by NASCOP. The delivery outcomes will include identification of efficient and cost-effective model of delivering PrEP in FP clinics, operationalization and adaptation of MoH/NASCOP PrEP delivery tools in FP clinics, counselling messages, flow charts/posters tailored for women in FP clinics and providers to work through prevention options, staffing requirements, and summaries of key scientific aspects learned during the implementation period. We will work with the national program in delivery of PrEP to optimize supply chain management of PrEP drugs, development and dissemination of provider guidelines and PrEP initiation/monitoring checklists, counselling guidelines, and clinician technical support. We will convene a national stakeholder meeting, including other parts of government and prevention providers, civil society, academia, and others to set the stage for next steps for full-scale implementation in FP clinics.

### **HUMAN SUBJECTS CONSIDERATIONS**

All program activities will be implemented through the standard routine FP clinic process. Screening of women for risk of acquiring HIV and provision of PrEP for those eligible and interested will be conducted as part of regular care in the PrEP program as stipulated by the Kenyan National Guidelines. Oral consenting will be implemented for all program activities as is the case for all standard of care services. Any individual who participates in the research component of the project, including provision of urine and blood samples to test for presence of tenofovir levels in the body, qualitative and quantitative surveys will provide an informed written consent. The consent forms will be translated into local languages.

The protocol, implementation plan, informed consent forms, data collection tools, and patient education materials will be reviewed and approved by the University of Washington Human Subjects Review Committee and the Kenyatta National Hospital-University of Nairobi Ethical Review Committee. Subsequent to initial review and approval, the responsible IRBs/ECs will review the program at least annually.

### ***Informed consent***

Informed consent will be conducted in a tiered fashion: oral consenting for routine program activities that directly impact patient care (all procedure key for provision of PrEP as standard of care, HIV testing and PrEP provision) and conducted as part of standard services. As is the case for all routine services, oral consenting for routine services will be done by the clinic providers. For all research procedures (i.e., urine, plasma and DBS samples

for drug levels, quantitative surveys, and qualitative interviews, phone/SMS support for adherence to PrEP) that are not directly routinely used for patient care but are important for overall program success and evaluation, written informed consent will be obtained before any procedure. Forms will be translated into local languages and verified by performing an independent back-translation.

### *Oral consenting for program activities*

Clinic delivery staff will perform oral consenting for all standard consent information describing programmatic rollout and standard procedures for Screening for HIV risk, PrEP counseling and delivery (i.e. HIV testing, promotion of male partner HIV testing, STI screening and treatment, PrEP prescription, program data abstraction, PrEP adherence support and clinic follow up). Consenting will cover any additional questions or concerns participants may have. All efforts will be made to ensure that women have a thorough understanding of the program and that their decision to be in the program is optional, and that not participating will not in any way affect their usual care. Every effort will be made to protect patient privacy and confidentiality to the extent possible and only authorized person may have access to program records.

### *Justification for oral consenting for program activities*

The goal of the program is to integrate PrEP delivery for HIV prevention as part of routine services offered to women receiving care in FP clinics in Kenya. Conducting oral consenting for non-research procedures in this program will be consistent with standard procedures implemented in providing routine services in the busy MCH and FP clinics in Kenya including provision of PMTCT, HIV testing, STI screening, immunization, and cervical cancer screening. The proposed program procedures will be part of routine HIV prevention services offered to women attending FP clinics. The procedures will represent no more than minimal risk and involves procedures for which consent would not normally be obtained outside the research context. The waiver of written consent will in no way affect the rights and welfare of the women receiving these services. We anticipate that utilizing oral consent will result in limited disruption of routine FP services and will facilitate seamless integration of PrEP counseling and delivery in family planning clinics, which is a key intervention area for the Kenya Ministry of Health HIV Prevention Revolution Road Map to maximize efficiency in service delivery through integration.

